### Data collection and management

Case report forms (CRFs) will be drafted to record original data collection regarding clinical information and assessment of outcomes. Paper copies of the CRFs will be filled in by the outcome assessors who are blinded to the group allocation of the participants. Microsoft Excel 2020 and EpiData 3.1 software will be used to manage data. The original clinical information and assessment of outcomes will be entered into EpiData. Double data entry and verification will be performed by two independent researchers to ensure the truthfulness and accuracy of the data. If there is an inconsistency of data input or missing data, the original participants’ data will be read again to further verify, and the verified data results will be exported to Excel.

### Statistical analysis

A sample size of 64 participants (32 per group) was determined to provide 90% power (*α* 0·05) to detect a mean FMA-UE difference of 11.0 (SD 9) points between the two treatment groups. The main analysis of this trial consists of a comparison of the outcomes after 3 weeks and at the end of follow-up (2 months). The statistician who is blinded to the group allocation of the participants will lock all data before statistical analysis. All data will be analysed with Social Sciences (SPSS) version 26.0 software (IBM Corporation, Armonk, USA) and GraphPad Prism version 9.0 software (GraphPad Software Inc., San Diego, USA). The baseline data and outcome analyses will be conducted on the full analysis set (FAS), using intent-to-treat (ITT) samples and completer samples. The per protocol set (PPS) will be used to analyse effective cases based on FAS. Furthermore, safety analysis will be performed on safety assessment set (SAS). Demographic data will be analysed using a two-sample *t*-test or Wilcoxon rank-sum test for continuous variables and the chi-squared test or Fisher’s exact test for categorical variables. For outcome, variables will be presented as the mean ± standard deviation ($$ \overline{x}\pm \mathrm{s} $$). Primary outcomes and secondary outcomes will be analysed using multivariable analysis of variance (ANOVA) for repeated measures, followed by Tukey's post hoc test. Statistical significance will be set at a *P value* less than 0.05.

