### Sample size

The sample size was estimated based on a comparison between the intervention group and the control group, represented by the improvement of the Fugl-Meyer Assessment of Upper Extremity (FMA-UE) as the primary outcome. In this study, a two-tailed test was chosen, *α* = 0.05. *μ*_*r*_ and *μ*_*c*_ represent the mean of FMA-LE scores after treatment in the intervention group (TCY-MIT + CRTs group) and the control group (CRTs group) respectively. *K* is the ratio of the sample size between the intervention group and the control group, so *K* = 1. According to the results of previous study [14], *μ*_*r*=_47.00, *μ*_*c*_=36.00, σ = 9, Δ = 3.6, *Z*_1 − *α*_= 1.96, and *Z*_1 − *β*_= 1.28. The calculated sample size of each group was approximately 32 individuals to achieve a power of 0.90 at a significance level of 0.05. After accounting for an anticipated dropout rate of 20%, the total number of patients required for this trial was 78, with 39 in each group. The formulas are as follows:
$$ {\displaystyle \begin{array}{c}{n}_r=\mathrm{K}{n}_c\\ {}{n}_c=\frac{{\left({Z}_{1-\alpha }+{Z}_{1-\beta}\right)}^2{\sigma}^2\left(1+\frac{1}{k}\right)}{{\left({\mu}_r-{\mu}_c-\Delta \right)}^2}\end{array}} $$

where *μ*_*r*_ is the mean of the intervention group, *μ*_*c*_ is the mean of the control group, *K* is the ratio of the sample size between the intervention group and the control group, Δ is the margin of superiority, and σ is the standard deviation.

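### The 90% power for 32 per group holds only against the 3.6-point superiority margin, but the Statistical analysis section restates it for an 11-point difference with no margin and plans an ordinary ANOVA

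*Protocol article*

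**What the plan says.** The Sample size section assumes post-treatment means of 47.00 and 36.00 and gives "σ = 9, Δ = 3.6". It explains that "Δ is the margin of superiority, and σ is the standard deviation", and its formula subtracts Δ from the difference in means before squaring. It also states "In this study, a two-tailed test was chosen", with Z values of 1.96 and 1.28. The result is reported as follows: "The calculated sample size of each group was approximately 32 individuals to achieve a power of 0.90".

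The Statistical analysis section opens by restating this: "A sample size of 64 participants (32 per group) was determined to provide 90% power" (α 0.05) "to detect a mean FMA-UE difference of 11.0 (SD 9) points between the two treatment groups". The margin is absent from that sentence. The same section then plans the test: "Primary outcomes and secondary outcomes will be analysed using multivariable analysis of variance (ANOVA) for repeated measures", with Tukey's post hoc test and significance at P below 0.05. The figure 3.6 appears nowhere outside the Sample size section. The section on the primary objective and study hypothesis says only that the combined treatment has a better effect than conventional therapy, with no amount attached.

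**The concern.** One sample size and one power figure are attached to two different hypotheses. The Sample size section describes a trial that must show a difference greater than 3.6 points. The Statistical analysis section describes a trial that must detect 11 points, and plans an analysis that, as ordinarily run, tests for no difference. These need very different numbers of patients, so the 90% cannot be right for both.

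Interpretation is also at stake. If the observed difference is moderate, one reader could call it superiority because P is below 0.05. Another, following the margin used for sizing, could say superiority was not shown. The plan should settle this before anyone has seen the data.

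**Working it through.** **Inputs.** From the Sample size section: means 47.00 and 36.00 (difference 11.0), SD 9, margin 3.6, Z = 1.96 and 1.28, 1:1 allocation. From the Statistical analysis section: 32 per group, 90% power, difference 11.0, SD 9, no margin. All power figures below are for a simple two-group comparison of means.

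**1. Reproduce the plan's figure, with the margin.**

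n per group = 2 × (1.96 + 1.28)² × 9² / (47 − 36 − 3.6)² = 1700.61 / 54.76 = 31.06, rounded up to 32.

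The Sample size arithmetic reproduces. The step from there to 39 per group for 20% dropout (31.06 / 0.8 = 38.8) is not at issue.

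**2. Repeat it as the Statistical analysis section words it, without the margin.**

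n per group = 1700.61 / 11² = 1700.61 / 121 = 14.05, so 15 by the normal approximation. With the noncentral t distribution, 15 per group gives 89.8% and 16 gives 91.7%. The requirement is therefore 15 to 16 per group, not 32.

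**3. Power of 32 per group.** The standard error of the difference is 9 × √(2/32) = 2.25.

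| Null hypothesis | Distance from null to true difference | Power (normal) | Power (noncentral t) |
|---|---|---|---|
| Difference = 0 | 11.0 | 99.8% | 99.8% |
| Difference = 3.6 | 11.0 − 3.6 = 7.4 | 90.8% | 89.9% |

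Only the second row matches the stated 90%. For the margin-free sentence to be true at 32 per group, the SD would have to be about 11 / (0.25 × 3.2416) = 13.6, not 9.

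**4. What 32 per group detects with 90% power against zero.** (1.96 + 1.2816) × 2.25 = 7.29 by the normal approximation, or about 7.4 by the noncentral t.

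**5. Where the two readings part.** The two-sided 5% critical value of t on 62 degrees of freedom is 2.00.

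- Significant against zero: observed difference of at least 2.00 × 2.25 = 4.5 points.
- Lower 95% confidence limit above 3.6: observed difference of at least 3.6 + 4.5 = 8.1 points.

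Between about 4.5 and 8.1 points the two sections lead to different statements. If all 39 per group are analysed, the standard error is 9 × √(2/39) = 2.04, and the limits are about 4.0 and 7.6 (normal approximation).

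**The case against.** The strongest reply is that the restatement is only a recap that dropped one input, that the error is in the safe direction, and that a condensed article may leave the decision rule to an analysis plan that is not shown. Much of this stands. Against zero the trial has more power than claimed, no patients need be added, and the absence of a written decision rule is not itself a fault here. What remains is that the restated sentence gives power, α, difference and SD. It is a complete calculation, and it does not yield 32 per group. A separate analysis plan cannot make it true.

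A reader might go further and infer that the success rule is wrong: if the true difference were exactly 3.6, a test against zero would be significant about 35% of the time at 32 per group, rather than 2.5%. The documents do not support calling that an error rate. The article states no success rule beyond a significance level, and its hypothesis is only that the combined treatment is better. Under that hypothesis a true 3.6-point difference is a real benefit, rejecting zero is correct, and the two-sided type I error stays at 5%. The margin may simply have been used to make the sizing conservative.

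Two cautions also stand. The null of zero is inferred from an ordinary ANOVA with no margin; it is not written out. The power figures above are not those of the planned repeated-measures ANOVA, which cannot be computed because the article gives no within-patient correlation.

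**Conclusion.** The Sample size and Statistical analysis sections contradict each other on what 32 per group delivers. The 90% is right for showing a difference greater than 3.6 points when the true difference is 11.0 (SD 9). As written in the Statistical analysis section it is wrong by about 10 percentage points: 99.8% against zero. The margin that fixed the sample size plays no part in the analysis described, so observed differences of about 4.5 to 8.1 points could be read either way.

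This rests on a two-group comparison with SD 9 and 32 per group, and on reading an ordinary ANOVA at P below 0.05 as a test of no difference. It does not show that testing against zero is invalid, nor that the trial is too small.

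**What to change.** Choose one of the following before data lock and make both sections agree.

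(a) **Keep the margin.** Reword the power sentence to: *32 per group gives 90% power to show a difference greater than 3.6 points if the true difference is 11.0 (SD 9).* State that superiority by that margin is concluded only if the lower limit of the two-sided 95% confidence interval for the between-group FMA-UE difference exceeds 3.6. Apply this at the time point or points the sponsor designates as primary; the article currently names both 3 weeks and 2 months for the main analysis, and this point gives no ground for choosing between them.

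(b) **Test against zero**, in line with the stated hypothesis. Remove the margin from the Sample size section and restate the power as about 99.8% for 11 points, or 90% for about 7.4 points. Label it as a two-group comparison with SD 9 and 32 per group, not as the power of the repeated-measures ANOVA.

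Either course costs only wording. Under (a) the bar for claiming superiority is higher; under (b) the stated power changes. The number randomised stays at 78.

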### Outcome measures and follow-up

Outcome measures will be performed by a certified, trained occupational therapist who is blinded to the group allocation of the participants. The assessments will be administered at baseline, after completion of the intervention (1, 2, and 3 weeks), and at the end of follow-up (2 months). Furthermore, resting-state fNIRS signal data collection will be a trained fNIRS technician.

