### Primary outcome measure

#### Motor function

The primary outcome measure is a change in score on the Fugl-Meyer Assessment of Upper Extremity (FMA-UE). The FMA-UE has been used to assess MIT-induced changes in upper extremity motor impairment in numerous RCTs [17, 18]. The acquired data are in the form of a 3-point ordinal scale (0 = cannot perform at all; 1 = can perform partially; 2 = can perform fully) that is calculated for each item [16]. The scale contains a total of 33 items, which are summed to provide the maximum score of 66. Assessors evaluated all participants immediately before therapy, after 3 weeks of therapy, and at the end of follow-up.

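### The plan names ITT and completer samples without saying which is primary, and repeated-measures ANOVA without imputation reduces the ITT analysis to completers

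*Protocol article*

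**What the plan says.** All references are to the protocol article.

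- **Populations** (Statistical analysis): "The baseline data and outcome analyses will be conducted on the full analysis set (FAS), using intent-to-treat (ITT) samples and completer samples". A further set is built on this one: "The per protocol set (PPS) will be used to analyse effective cases based on FAS". Neither sentence ranks the samples.
- **Method** (same section): "Primary outcomes and secondary outcomes will be analysed using multivariable analysis of variance (ANOVA) for repeated measures, followed by Tukey's post hoc test".
- **Time points** (same section): "The main analysis of this trial consists of a comparison of the outcomes after 3 weeks and at the end of follow-up (2 months".
- **Visits**: Outcome measures and follow-up lists five: baseline, weeks 1, 2 and 3, and 2 months. The primary outcome's own section (Motor function) lists three: "Assessors evaluated all participants immediately before therapy, after 3 weeks of therapy, and at the end of follow-up".
- **Dropout** (Sample size): a 20% allowance raises about 32 per group to 39 per group, 78 in total.
- **Missing data** (Data collection and management): the only step given is to go back to the source record. That resolves entry errors but cannot supply a visit that never took place.

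**The concern.** An ITT sample and a completer sample contain different people whenever anyone is lost. If both are reported and neither is primary, two answers exist and the plan does not say which decides the trial.

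The named method adds a second problem. Classical repeated-measures ANOVA, in its split-plot or multivariate form, needs a value at every modelled visit and deletes the whole participant otherwise. The main comparison covers both 3 weeks and 2 months. With both in one model, a person who completed treatment and was assessed at week 3 but missed the 2-month visit leaves the week-3 comparison too. Without imputation, the ITT label then adds nothing to the completer label.

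At stake is the protection that randomisation gives. Completers are a group selected after randomisation, and if the reasons for loss differ between arms, the group difference among completers is biased.

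**Working it through.** **1. The plan's own figure.** Inputs from Sample size: means 47.00 and 36.00, margin 3.6, SD 9, Z values 1.96 and 1.28, K = 1.

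n per group = (1.96 + 1.28)² × 9² × 2 / (47 − 36 − 3.6)² = 10.4976 × 162 / 54.76 = 31.06, rounded up to 32. This reproduces. For dropout, 31.06 / 0.8 = 38.8, so 39 per group and 78 in total. (32 / 0.8 would give 40; the gap is immaterial here.)

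**2. How many people are affected.** At the 20% allowance, 0.8 × 78 = 62.4 have complete data and 78 − 62.4 = 15.6, about 16, are dropped.

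**3. Power among completers.** With 31.2 per group, an effective difference of 11 − 3.6 = 7.4, SD 9 and two-sided 0.05, power is 0.901. With all 39 per group it is 0.953. The inflation does what it was meant to do.

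**4. Which visits count.** If weeks 1 and 2 are modelled as well, four post-baseline visits must all be present; on the shorter FMA-UE schedule, only two. With independent missingness per visit (assumed), complete records out of 78 are:

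| Missing per visit | Two visits | Four visits |
|---|---|---|
| 2% | 74.9 | 71.9 |
| 5% | 70.4 | 63.5 |
| 10% | 63.2 | 51.2 |

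**5. Size of a possible bias.** The documents give no dropout mechanism, so these inputs are assumptions:

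- SD 9 at each visit, with equal correlation ρ between visits of 0.5, 0.7 or 0.85.
- The outcome is change from baseline, so its SD is 9 × √(2(1 − ρ)) = 9.0, 7.0 or 4.9.
- 20% of each arm is lost after week 3.
- In the intervention arm, the log-odds of loss rise by k per SD of smaller week-3 gain. In the control arm, loss is random.

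Shift in the completer difference, in FMA-UE points, from a simulation of 1,000,000 in the intervention arm (random loss leaves controls unbiased):

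| ρ | k = 0.25, week 3 | k = 0.25, 2 months | k = 1, week 3 | k = 1, 2 months |
|---|---|---|---|---|
| 0.5 | 0.46 | 0.22 | 1.56 | 0.78 |
| 0.7 | 0.35 | 0.17 | 1.21 | 0.61 |
| 0.85 | 0.24 | 0.11 | 0.85 | 0.42 |

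Because loss depends on gain relative to the arm's own mean, these shifts do not depend on the true difference. Against the 11.0 points the plan expects, the strong case at week 3 is 0.85 / 11 = 8% to 1.56 / 11 = 14%.

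**6. Limits of the illustration.** With the same mechanism in both arms, the shifts cancel and the bias is essentially zero. If raw visit scores are compared instead of changes, the strong case gives about 0.4 to 0.8 points at week 3 and about none at 2 months. A likelihood-type estimate using all observed visits recovers the true difference at both times under this mechanism.

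**The case against.** **The sentence can be read as two analyses**, ITT plus a completer companion, and naming them separately suggests the authors expect them to differ. This is fair: the text says the analyses use both samples, not that the full analysis set is defined as both. What stands is that, even on this reading, neither is named as primary.

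**Imputation may be specified elsewhere.** A journal article commonly leaves missing-data handling to the full protocol or SAP, which are not shown, so its absence here is no finding. What stands is the combination the article does state: an ITT sample analysed by "multivariable analysis of variance (ANOVA) for repeated measures". That method cannot keep incomplete participants unless something further is done first.

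**The bias depends on chosen inputs.** It needs informative loss that differs by arm. A reader might infer that participants know their arm and leave accordingly. The Randomization and blinding section says they do not know it. Only one arm receives the Tai Chi video and guided imagery (Intervention group), which makes that claim doubtful, but the documents do not establish unblinding or arm-related loss. The bias figures are illustrations, not predictions.

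**The 20% is an allowance in the sample size**, not a forecast of who will be missing from the analysis. This stands, and completers alone still give about 90% power.

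**Conclusion.** The point holds in conditional form. The plan names two samples without saying which is decisive, and its chosen method, run without imputation, makes them the same sample and discards week-3 scores already collected: about 16 of 78 participants at the allowance introduced by "After accounting for an anticipated dropout rate of 20" percent.

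The consequence is possible bias, not lost power. It ranges from none, if loss follows the same mechanism in both arms, to about 0.3 to 0.5 points (weak selection) or 0.9 to 1.6 points (strong selection) at week 3 if informative loss is confined to one arm. It is smaller at 2 months under the same assumptions. These figures rest on the assumed SD, correlations, timing of loss and selection strength.

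A reader might go further and conclude that the reported ITT result will certainly be a completer result, or that it will be biased. The documents support neither: the first depends on no imputation being done, the second on an arm-specific loss pattern that nothing in the article shows.

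**What to change.** 1. Name all randomised participants, analysed as allocated, as the single primary set for the primary conclusion.
2. Replace repeated-measures ANOVA with a likelihood-based mixed model for repeated measures on all observed visits, with group contrasts at 3 weeks and 2 months. Participants with partial follow-up then contribute what was observed. SPSS 26, already named in the plan, can fit it. Imputation before the planned ANOVA would also retain participants, but it would have to be specified.
3. Label completer and per-protocol results as sensitivity analyses.
4. Reconcile the two FMA-UE visit schedules, so that it is clear which visits enter the model.

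The cost is revised wording and slightly more analysis work. The mixed model relies on a missing-at-random assumption: loss may depend on scores already observed but, given those, not on the unseen ones. That assumption should be stated.

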### Eligibility criteria

#### Inclusion criteria

First event of stroke (infarct or haemorrhage) and in line with the diagnostic criteria of cerebrovascular disease formulated by the 4th National Cerebrovascular Academic Conference, confirmed by CT or MRI;No gender limitation, age 40 to 80 years;Poststroke duration 3 to 6 months;For pure motor hemiplegia, the degree of affected upper and hand is Brunnstrom grade II–VI;Good MI ability assessed by the Kinesthetic and Visual Imagery Questionnaire (KVIQ-20) ≥ 25;Right-handed, as determined by the Edinburgh Handedness Inventory;Agreement of the patient or his or her legal guardian (if necessary) to voluntarily participate in the study and signed informed consent. Able to understand and implement rehabilitation training.

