### Randomization and blinding

All eligible participants will be randomly assigned to two groups in a 1:1 ratio. The computer-generated randomization sequence numbers will be generated using the Statistical Package for the Social Sciences (SPSS) 26.0 statistical software. This work will be performed by an occupational therapist not involved in this trial and kept in sealed envelopes. The occupational therapist will assign participants to the two groups according to the random sequence.

To minimize the source of bias after randomization, we will take the following method during this research: conventional rehabilitation therapists and participants will not have any information about the purpose of this study and whether other treatments will be conducted. Meanwhile, TCY-MIT will be guided by another therapist who will not know whether the patients’ participating in other therapies. Furthermore, participants and research personnel do not know the allocated group. The outcome assessor would not be involved in the whole therapy process. Additionally, to examine the success or failure of blinding, an assessor will be evaluated by calculating new blinding index (BI) [15]. They will be inquired which group do they think patients take part in and choose one item from the following answers: CRTs group, TCY-MIT group, or unknown. The new BI is scaled to an interval of − 1 to 1 (0 = consistent with perfect blinding; 1 = complete lack of blinding; -1 = opposite guessing which may be related to unblinding). If a higher-than-expected proportion guesses correctly, a discussion will be made concerning the potential biases causing partial unblinding.

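### The repeated-measures ANOVA with Tukey's test does not say which between-group effect decides superiority, and it names no baseline covariate; one baseline-adjusted model would settle both at no cost

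*Protocol article*

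**What the plan says.** The Statistical analysis section fixes one method for every outcome: "Primary outcomes and secondary outcomes will be analysed using multivariable analysis of variance (ANOVA) for repeated measures", "followed by Tukey's post hoc test", with significance at P below 0.05. It does not say whether the group effect, the group-by-time effect or a group difference at one visit is the test of the hypothesis, and it lists no covariate.

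On timing, the same section says: "The main analysis of this trial consists of a comparison of the outcomes after 3 weeks and at the end of follow-up (2 months"). Neither time point is ranked above the other.

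The Motor function section defines the endpoint: "The primary outcome measure is a change in score on the Fugl-Meyer Assessment of Upper Extremity (FMA-UE"). It gives three assessment times: "Assessors evaluated all participants immediately before therapy, after 3 weeks of therapy, and at the end of follow-up". The section on outcome measures and follow-up gives five: "The assessments will be administered at baseline, after completion of the intervention (1, 2, and 3 weeks), and at the end of follow-up (2 months").

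There are two arms: "All eligible participants will be randomly assigned to two groups in a 1:1 ratio". Eligibility is wide in severity: "the degree of affected upper and hand is Brunnstrom grade II–VI". The Sample size section sizes the trial on the difference between two post-treatment means, with no baseline term.

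**The concern.** A repeated-measures ANOVA on two groups produces a group test, a time test and a group-by-time test. They answer different questions and can disagree. A plan that names the model but not the deciding effect leaves that choice open until the data are seen.

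Tukey's procedure does not close the gap. Between two groups there is one pair, so it changes nothing. Across visits within a group it tests change over time, which does not address superiority. Across all group-by-visit cells it does include the 3-week group comparison, but it charges that comparison for many pairs of no interest.

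Baseline FMA-UE is scheduled for everyone and probably varies widely, given the Brunnstrom range admitted. It is an obvious covariate, and the plan does not use it as one. At stake are the clarity of the primary test, some power under certain readings, and some precision under all of them.

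**Working it through.** **Inputs from the protocol article.** Post-treatment means 47 and 36 (difference 11), SD 9, margin 3.6, two-sided alpha 0.05, power 0.90, 32 per arm (Sample size); difference restated as 11.0, SD 9, without the margin (Statistical analysis); three or five visits (as above).

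**Assumptions, not in the document.** Equal correlation rho between visits, taken over 0.5 to 0.9; SD 9 at every visit; the same group difference at 3 weeks and 2 months; for five visits, a linear build-up over weeks 1 to 3. Power uses the normal approximation, Φ(effect/SE − critical value).

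**1. The plan's own figure.** n = (1.96 + 1.28)² × 81 × 2 / (11 − 3.6)² = 10.498 × 162 / 54.76 = 31.06, so 32 per arm. This reproduces. It describes an unadjusted comparison of two post-treatment means: SE = 9 × √(2/32) = 2.25, and power at 7.4 is Φ(7.4/2.25 − 1.96) = 90.8%.

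**2. Tukey.** The critical value is the 95% studentized-range point divided by √2. Power is for the 3-week post-score contrast at 7.4 points.

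| Means compared | Pairs | Critical value | Power |
|---|---|---|---|
| 2 (the groups) | 1 | 1.96 | 90.8% |
| 6 (2 groups × 3 visits) | 15 | 2.85 | 67% |
| 10 (2 groups × 5 visits) | 45 | 3.16 | 55% |

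At 11 points, 11/2.25 = 4.89. Power is then Φ(4.89 − 2.85) = 98% or Φ(4.89 − 3.16) = 96%.

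**3. Group main effect, baseline included as a time level.** The effect is the average over k visits, and SE = √[(2/32) × 81 × (1 + (k − 1)rho)/k].

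- Three visits, 11 points: (0 + 11 + 11)/3 = 7.33. For 7.4 points: 14.8/3 = 4.93.
- Five visits, 11 points: (0 + 3.67 + 7.33 + 11 + 11)/5 = 6.6. For 7.4 points: 4.44.
- At rho 0.8, SE = √(5.0625 × 2.6/3) = 2.09 for three visits and √(5.0625 × 4.2/5) = 2.06 for five.

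| True difference | Visits | Power, rho 0.8 | Power, rho 0.5 to 0.9 |
|---|---|---|---|
| 7.4 | 3 | 65% | 77% to 62% |
| 7.4 | 5 | 58% | 72% to 54% |
| 11 | 3 | 94% | 98% to 92% |
| 11 | 5 | 89% | 97% to 86% |

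**4. Change score, or the group-by-time contrast from baseline to 3 weeks.** These are the same comparison, and the effect is undiluted. Relative to the unadjusted post score, the variance factor is 2(1 − rho) for change and 1 − rho² for ANCOVA. Their ratio is 2/(1 + rho).

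- rho 0.6: 2/1.6 = 1.25, so change-score variance is 25% larger than ANCOVA's.
- rho 0.8: 2/1.8 = 1.11, so it is 11% larger.
- At the ends of the range, rho 0.5 gives 33% and rho 0.9 gives 5%.
- Change-score SE is 2.25 × √0.8 = 2.01 at rho 0.6 (power about 96% at 7.4) and 2.25 × √0.4 = 1.42 at rho 0.8 (over 99%). The ANCOVA SE at rho 0.8 is 2.25 × √0.36 = 1.35.

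**The case against.** A reader might infer that the planned ANOVA necessarily dilutes the treatment effect. The article does not support that. Dilution needs two things it never states: that the group main effect is the test, and that baseline is a level of the time factor. The change endpoint in the Motor function section, and a main analysis framed around 3 weeks and 2 months, point rather the other way. This part of the objection stands, so the dilution figures are conditional.

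A reader might also infer that baseline is ignored. It is not, if a change score or a group-by-time contrast is used, because both subtract it. What is absent is covariate adjustment. On the change reading, at correlations of 0.6 to 0.8, the trial exceeds its planned power, so the loss against ANCOVA does not endanger the design. The word multivariable might hint at covariates, but none is named, and the abbreviation list uses the phrase only to expand ANOVA.

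The 65% and 58% figures use 7.4 points, the distance in the sample-size formula. The Statistical analysis section restates the target as 11.0, where even the main-effect reading keeps about 94% or 89%. That is a fair correction to any impression of a badly underpowered analysis.

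Finally, model details are often left to an analysis plan that is not shown here. That would excuse silence. It does not excuse a method that is stated, and Tukey is stated for a two-arm trial in which it is either redundant or costly.

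**Conclusion.** The point holds as a should-fix. The article commits all outcomes to repeated-measures ANOVA plus Tukey without naming the effect that tests superiority, and without a baseline covariate. The 3-week time point is named, but it is not ranked against 2 months or tied to a model contrast.

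The consequence depends on the reading. It ranges from a modest efficiency loss (change-score variance 25% to 11% above ANCOVA's at correlations of 0.6 to 0.8) to a material power loss if Tukey is run over all cells or the main effect is tested with baseline as a level. Those larger losses apply mainly at 7.4 points. The correlation, the common SD and the build-up over weeks 1 to 3 are assumptions. Nothing here shows bias or type I error inflation, so it would be wrong to conclude that the primary result would be invalid as planned.

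**What to change.** Replace the ANOVA and Tukey sentence with one model, for example:

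> FMA-UE at the post-baseline visits will be analysed with a linear mixed model containing treatment, visit, treatment-by-visit, baseline FMA-UE and baseline-by-visit. The primary contrast is the between-group difference at 3 weeks, with its 95% confidence interval. The difference at 2 months is the next contrast, from the same model.

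Three weeks is proposed as primary because it is the end of treatment and matches the post-treatment means on which the trial was sized; the 2-month comparison is kept. Delete Tukey. Use the same model, with each outcome's own baseline, for the Box and Block Test, grip, pinch and modified Barthel index. The fNIRS correlation outcome needs its own specification and is outside this change. State whether FMA-UE has three or five assessments, since that fixes the visits in the model.

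The cost is a wording change. The planned software fits the model, and no extra data or patients are needed.
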